## Abstract

**Background:**

As early as pregnancy, maternal mental stress impinges on the child’s development and health. Thus, this may cause enhanced risk for premature birth, lowered fetal growth, and lower fetal birth weight as well as enhanced levels of the stress hormone cortisol and lowered levels of the bonding hormone oxytocin. Maternal stress further reduces maternal sensitivity for the child’s needs which impairs the mother-child-interaction and bonding. Therefore, prevention and intervention studies on mental stress are necessary, beginning prenatally and applying rigorous research methodology, such as randomized controlled trials, to ensure high validity.

**Methods:**

A randomized controlled trial is used to assess the impact of psychotherapy and telemedicine on maternal mental stress and the child’s mental and physical health. Mentally stressed pregnant women are randomized to an intervention (IG) and a not intervened control group. The IG receives an individualized psychotherapy starting prenatal and lasting for 10 months. Afterwards, a second randomization is used to investigate whether the use of telemedicine can stabilize the therapeutic effects. Using ecological momentary assessments and video recordings, the transfer into daily life, maternal sensitivity and mother-child-bonding are assessed. Psycho-biologically, the synchronicity of cortisol and oxytocin levels between mother and child are assessed as well as the peptidome of the colostrum and breast milk, which are assumed to be essential for the adaptation to the extra-uterine environment. All assessments are compared to an additional control group of healthy women. Finally, the results of the study will lead to the development of a qualification measure for health professionals to detect mental stress, to treat it with low-level interventions and to refer those women with high stress levels to mental health professionals.

**Discussion:**

The study aims to prevent the transgenerational transfer of psychiatric and somatic disorders from the mother to her child. The effects of the psychotherapy will be stabilized through telemedicine and long-term impacts on the child’s and mothers’ mental health are enhanced. The combination of psychotherapy, telemedicine and methodologies of ecological momentary assessment, video recording and bio banking are new in content-related and methodological manner.

**Trial registration:**

German Clinical Trials Register: DRKS00017065. Registered 02 May 2019. World Health Organization, Universal Trial Number: U1111–1230-9826. Registered 01 April 2019.

## Background

Perinatal stress and mental strain can impact negatively on the mother’s and the offspring’s mental as well as physical health. Hormonal changes, critical life events and socio-economic disadvantages like unemployment, poverty and discrimination increase emotional distress and the risk of psychiatric disorders during pregnancy [1–4].

The WHO reports an estimated 10% of mental disorders worldwide during pregnancy, 15.6% in developing countries. The percentages are even higher after childbirth [5]. Reimbursement data of a German statutory health insurance demonstrates that 43.6% of pregnant women received at least one psychiatric diagnosis. Antenatal depression affects 9.3% of women, anxiety 16.9%, somatoform/dissociative disorders 24.2%, and acute stress reactions 11.7% [6]. These data concur with those of international studies reporting prevalence rates for antenatal depression of 11% and for anxiety disorders of 15% [7]. Moreover, pregnancy itself seems to be a sensitive time for the development of mental disorders, as the prevalence of depression is higher in the third (12.0%) and in the second (12.8%) than in the first trimester (7.4%) [8]. Women suffering from mental disorders also display poorer physical health, with higher risk of preeclampsia, reduced sleep, increased substance use, elevated cortisol levels and below-average weight gains [9–12].

In addition to the burden on pregnant women, maternal stress and mental disorders during pregnancy also affect birth outcomes as well as the physical health and the cognitive development of the offspring via intergenerational transmission processes. This transgenerational transmission occurs via placental blood exchange, fetal adaptation processes, epigenetic and hormonal programming, circumstances of the birth and impaired mother-offspring interactions [13–15]. It is supposed that elevated cortisol levels in stressed pregnant women may cause placental hypofusion and increased fetal circulation of glucocorticoid which impact on fetal development [3, 15]. This raises the risk of fetal growth restriction, preterm births and lower fetal birth weight [16–20]. Low birth weight neonates therefore exhibit an increased risk for diagnosis of infectious diseases, strokes, obesity, cancers, mental and behavioral disorders [21, 22].

Moreover, due to the maternal mental stress, the sensitivity for the emotional and developmental needs of the offspring is reduced which impairs mother-child-interaction and the bonding process [23–26]. Consequently, the social, psychological and cognitive child development is impaired associated with an increased risk for the child to develop own psychiatric and somatic disorders [27–32]. Recent studies examining this transgenerational transmission of disorders report that infants of mothers with antenatal and prenatal psychiatric disorders are at higher risk for regulatory disorders, ADHD, conduct disorders, elevated cortisol reactions to stress as well as impaired attachment styles and heightened hypochondriacal symptoms [12, 33–41].

### Prevention and intervention of prenatal and postpartum mental stress

These interdependencies raise the question how maternal mental health can be improved and how maternal distress and mental disorders can be prevented. A Cochrane Review provides evidence that psychotherapeutic and psychosocial interventions for postpartum depression lead to a reduction of depressive symptomatology of 30% [42]. Especially cognitive-behavioral therapy (CBT), individual treatments and a start of interventions in late pregnancy are effective for treating and preventing depressive symptoms perinatal and postpartum [43–46]. Additionally, CBT is effective in clinical settings as well as community samples, in women with severe as well as mild depressive symptoms [45].

Separate components of cognitive therapy have been proven as effective as long-term CBT: women with preterm infants and financial hardship reported fewer depressive episodes and symptoms after problem-solving education [47]. Another prenatal intervention study implemented a depression, anxiety and parenting preparation program. Women received a community networking booklet and a self-help support workbook with regular individual telemedical support. The workbook was constructed to correspond to the telephone calls, for example, regarding instructions about problem-solving skills, the strengthening of protective factors and the reduction of risk factors. Women of the intervention group scored lower in levels of depression, anxiety, stress and parenting dysfunction as women in the routine care group [48]. In addition, there are several short-term interventions based on cognitive-behavioral therapy proven to be effective, for example interpersonal psychotherapy [46, 49] and mindfulness-based cognitive therapy [50, 51].

Research around fetal programming recommends intervention starts as early as possible, that means on preconception or in pregnancy [15, 52].

It can be summarized that pregnancy and the postpartum period are stages of life with increased risk to develop mental disorders. Prenatal und postpartum intervention programs have effects on mental health in reducing stress and depressive symptoms [53]. But there are manifold barriers for women to access treatments [54–56].

### Barriers to treatment seeking among pregnant women

Primarily, prevalence rates of mental disorders are high, but detection rates are generally low [57]. Thus, midwifes and obstetricians need to be trained to detect mental health problems and to offer support [52]. Socio-economically disadvantaged women living in rural areas are twice as likely affected by mental disorders, but for these women in particular it is difficult to engage and retain treatments [49, 58]. Time constraints, access to transportation, need for childcare, financial pressure are just some of those obstacles. Short-term interventions with the possibility of home visits are therefore prone to be more effective in this population [49, 52]. Telemedical interventions are welcome opportunities to support mentally stressed women on-site in their every-day life [48, 59–61]. Thus, a combination of cognitive behavioral therapy and telemedical follow-up intervention seems to be promising in treating maternal mental stress.

### Research agenda of the current study (PriVileG-M trial)

The study PriVileG-M focuses on a population of women living in a rural area (Western Pomerania in Northern Germany) with high rates of unemployment and poverty [62]. Mentally stressed women are detected during pregnancy by short screening questionnaires in midwife or obstetrician surgeries during standard medical examinations, and receive a psychotherapeutic CBT short-intervention with subsequent telemedical support. Thus, the study offers individualized visiting support rather than waiting for the concerned to ask for help.

Limits of previous studies exploring intervention effects on prenatal and postpartum mental health are small sample sizes, non-random designs, lack of control groups and an absence of follow-up data [63]. PriVileG-M is therefore conceptualized as a sequentially randomized controlled trial with a randomized control group of mentally stressed women receiving no intervention and an additional, non-randomized control group of mentally healthy pregnant women. The intervention group receives a psychotherapeutic treatment. Approximately 10 months after baseline, the intervention group is randomized again in two groups with and without telemedical intervention. Women are monitored through prenatal and postpartum period by four follow-ups, the last occurring 1 year after birth. Following the interventional study, a qualification measure will be designed. Health professionals who regularly are in touch with pregnant women (e.g., midwives, nurses, social workers) are trained to detect mental disease symptoms, to relieve their psychiatric strain and to refer to mental health professionals if necessary. The aim is to detect mental stress and to offer treatment as early as possible. Thus, mental stress in mothers and children might be reduced and long-term effects prevented. During the qualification measure, basic knowledge about psychiatric diseases, existing supply structures and therapy options are taught. Therefore, specific themes raised during the intervention study will be extracted and discussed. Further, short, easy to learn and customizable interventions will be taught, for instance, emotional and stress regulation, social skills training or relaxation techniques.

### Objectives

The present study examines the impact of individualized psychotherapy and telemedicine on prenatal and postnatal stress and mental health via a sequentially randomized controlled trial. The study aims to explore, and ideally prevent, transgenerational transfer of physical and mental stress and disorders from the mother to her child. Moreover, the results will be used to develop a teaching course for professionals that work with pregnant women and young mothers (e.g., social workers, midwives, nurses) to help them in recognizing symptoms of mental illness and offering or referring to appropriate care.

#### Primary outcomes

(1) Concerning the women, interventions are expected
i.to reduce mental stress and to improve mental health and quality of lifeii.to enhance self-awareness, self-confidence, self-efficacy and resilience

(2) Concerning the children, interventions are expected
i.to reduce rates of preterm birth as well as complications during childbirthii.to reduce regulation disorders in childreniii.to reduce cognitive, physical and psychomotor retardationsiv.to reduce infectious diseases and low fetal birth weight

(3) Concerning women and children, interventions are expected
i.to improve mother-child-interaction and to strengthen bondingii.to lower cortisol levels in both mother and child

The outcomes (1) to (3) are expected in the groups of mentally stressed mothers to converge to those of healthy mothers and children in the non-randomized control group at the end of the study. In contrast, it is assumed that these outcomes differ from the control group of stressed women without intervention from those of the intervention group.

(4) In addition, the results of the study will lead to the development of a qualification measure for health professionals who will be trained to detect mental stress, and in turn to refer those women to mental health professionals.

#### Secondary outcomes

The study also aims to examine hormonal transmissions between mother and child to explore neurobiological mechanisms of transgenerational transmission. Therefore, a biobank will be built up to analyze DNA-sequences, RNA-expression, miRNA as well as DNA methylation and other metabolomics. In particular, the study scrutinizes how the development of the HPA-axis in infants is shaped by depressive symptoms of the mother and how the HPA-axis in mother and infants is influenced by the different interventions of the study. Moreover, in exploratory analyses, the constituents of breast milk will be analyzed. It is hypothesized that oxytocin levels will increase and melatonin levels will decrease in both stressed mothers and child after treatments. Finally, it is assumed that the intervention increases rates of breastfeeding mothers in the intervention group.

## Methods/design

Pregnant women are screened in midwife or obstetrician surgeries. On the basis of the screening results, the women are assigned to the group of healthy or to the group of mentally stressed women. While the healthy group serves as an additional control group (HCG) over the course of the study, the group of mentally stressed women will be randomized in two steps. In a first step of the randomization process, mentally stressed women are randomized to a psychotherapeutic intervention group (PIG) or a psychotherapeutic control group (PCG) with usual care. In a second step following the psychotherapeutic intervention, women of the PIG are randomized to a subsequent telemedical intervention (TIG) or a telemedical control group (TCG). All participants will be assessed at five time points: baseline (prenatal), around the delivery, 8 weeks, 26 weeks and 52 weeks postpartum (see Table 1). The SPIRIT statement for clinical trial protocols is used to report methods and procedure of this study.

**Table 1 Tab1:** Questionnaires and items employed at the different study assessments

Study Assessments	Measures	Study time points						
		S1	S2	BL^a^	0W	8W	26W	52 W
Socio-demographic	Date of birth of the mother	X						
	Date of birth of the infant	X						
	Week of gestation	X	X	X				
	Educational attainment	X		X				
	Marital status	X		X				
	Indigenous status			X				
	Profession			X				
Medical								
Physical health of the mother	Medical documentation of the mother from the German Mutterpass				X			
	Alcohol, Smoking and other Lifestyle habits, chronic diseases, pregnancy related diseases			X	X	X	X	X
	Documentation of medication using Brown bag review			X				
Physical health of the infant	Child’s medical records, the Geman U-Untersuchungs-Heft filled in by pediatrician					X	X	X
	Semi structured health interview including number of infectious diseases, chronic disease use of antibiotics.					X	X	X
	Brown bag review for medication					X	X	X
	Anthropometric measures including length, weight, and head circumference					X	X	X
	physical examination of the infant					X	X	
Infant General Development	Neuropsychologic Development Screening (NES)					X	X	X
Infant behavior	German questionnaire about crying, feeding and sleeping behavior (SFS)					X	X	
	Infant Behavior Questionnaire (IBQ-R)					X	X	X
Breastfeeding Rate	Questionnaire about breastfeeding rates and times					X	X	X
Psychological								
Stress Symptoms	Brief Symptom Inventory (BSI-18)	X	X	X		X	X	X
	Coping Inventory for Stressful Situations (CISS)			X				X
	questionnaire about chronic stress (TICS)			X				X
	Recognition of stress-factors (KFB)			X		X	X	X
Resilience	RS-11			X		X	X	X
Mental Health								
Mental Disorders	Diagnostic Interview for Mental Disorders (DIPS)		X					
Trauma	Childhood Trauma Questionnaire (CTQ)			X				
Dissociation	Dissociative Experiences Scale-Taxon (DES-T)			X			X	X
Depression	Patient Health Questionnaire (PHQ-9)			X		X	X	X
	Edinburgh Postnatal Depression Scale (EPDS)			X	X	X	X	X
Worries	Penn State Worry Questionnaire (PSWQ)			X		X	X	X
	Cambridge Worry Scale (CWS)			X				
Personality Traits	NEO-FFI			X				X
Social network	short partnership questionnaire (PFB-K)			X				
	Perceived Social Support Questionnaire (F-SozU-6)			X		X	X	X
Attachment in adults	Experiences in Close Relationships - Revised (ECR−RD 12)			X				
	Revised Adult Attachment Scale (AAS-R)			X				
Prenatal attachment	Maternal Antenatal Attachment Scale (MAAS)			X				
Postpartum attachment	Postpartum Bonding Questionnaire (PBQ)					X	X	X
Video assessments								
Attachment	Mother-child interaction					X	X	
Ecological Momentary Assessment								
Mental state	Multidimensional Mood Questionnaire (MDMQ)			X			X	X
	stress level			X			X	X
Physical health	self-related health of the mother			X			X	X
	Of the infant						X	X
Mother-child-interaction	Modified items of the PBQ						X	X
	Modified item of the self-assessment questionnaire about mother-child-interaction (SF-MKI)						X	X
Mother-child-bonding	Modified items of the MAAS			X			X	X
Child sleeping behavior	Modified items of the regulation disorders questionnaire (SFS)						X	X
Laboratory								
Saliva Cortisol Mother and Infant	At midday collection during visit			X		X	X	
	Morning and evening Saliva cortisol from 3 different days					X	X	
Saliva Melatonin	Saliva melatonin at midday during the visit			X		X	X	
	Morning and evening Saliva Melatonin from 3 different days					X	X	
Urin sample Mother and Infant	Analysis of metabolics and oxytocin			X		X	X	
Bloodsample of the mother	Full blood analysis including complete blood count, electrolytes, glucose, kidney function, liver, thyroid and inflammatory values			X			X	
	Mothers Epigenetics			X			X	
Cordblood	Infants Epigenetics				X			
Colostrum	Composition of Colostrum, Peptidom				X			
Breast milk	Composition of Mothermilk, Peptidom					X	X	
Evaluative Assessments								
Qualitative interviews	Structured individual interviews about the contentment of the treatment result, perceived benefits and changes					X	X	X
Quantitative questionnaires	expectations in the study			X				X
	perceived benefits of the study and the quality of the interventions					X	X	X
	impact of the telemedical intervention on quality of life							X
	study evaluation							X
Documentation								
Therapeutic process^a^	date, time, home visit or not, woman appeared or not, treatment focus, course of content, changes since the last consultation, agreements and homeworks, interactions, hypotheses, discussed topics, therapeutical interventions							
Telemedical process^a^	date, time of day, duration of the call, circumstances of the call							

Note: S1 = Screening1, S2 = Screening2, BL = Baseline (occurs at approximately 25-28 weeks gestation), 0W = delivery, 8W = 8-weeks-follow-up, 26W = 26-weeks-follow-up, 52W = 52-weeks-follow-up, ^a^documentation of the treatment process (therapeutical and telemedical) do not occur at follow-ups, but over the period of the treatment at each consultation

### Study participants

#### Power and sample size

The primary outcome criterion of the study is to reduce mental stress of the women assessed by the brief symptom inventory (BSI-18). Former research reported healthy women to have a BSI-18 total score of 3–4 points, whereas mentally stressed women had 15–25 points [64]. After psychotherapy the BSI-18 total score was reduced by 10 points [65, 66]. Hence, assuming a medium effect size (Cohen’s d = 0.5 corresponding to a reduction by 7 points), a test-retest correlation of 0.5 between the baseline assessment and 26-week-follow-up, a significance level α = 0.05 and a power of β = 0.80, 27 women are required in each group. As telemedicine is an add-on focusing on stabilizing the effects of the psychotherapy, the second randomization into TIG and TCG is neglected in this calculation. However, envisaging 80 women for each group and assuming a drop-out-rate of 10%, 36 women are randomized to the TIG and TCG which is enough to analyze medium to large effects. Figure 1 shows the participant flow and the sample sizes of the different study groups.

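### The protocol calls a long list of maternal and infant outcomes primary in one section and the BSI-18 alone in another, with differing time points; its alpha and power cover the BSI-18 only

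*Protocol article*

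**What the plan says.** All places are in the protocol article.

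- **Power and sample size** names one endpoint: "The primary outcome criterion of the study is to reduce mental stress of the women assessed by the brief symptom inventory (BSI-18"). The assumptions given are "d = 0.5 corresponding to a reduction by 7 points" and "a test-retest correlation of 0.5 between the baseline assessment and 26-week-follow-up". The result is "a significance level α = 0.05 and a power of β = 0.80, 27 women are required in each group". The plan is then to enrol 80 per group with 10% drop-out.
- **Objectives, Primary outcomes** has eight sub-items in three blocks (women, children, both). They run from maternal stress, mental health and quality of life, through "to enhance self-awareness, self-confidence, self-efficacy and resilience" and "to reduce infectious diseases and low fetal birth weight", to "to lower cortisol levels in both mother and child". Item (4) is a training measure for health professionals. Below the list, outcomes (1) to (3) are expected to approach those of healthy mothers and children by the end of the study, and "it is assumed that these outcomes differ from the control group of stressed women without intervention from those of the intervention group".
- **Secondary outcomes** covers hormonal transmission, the biobank, breast-milk constituents, oxytocin and melatonin, and breastfeeding rates. It does not demote any of the listed primary items.
- **Table 1** schedules the BSI-18 at baseline and at 8, 26 and 52 weeks. Saliva cortisol and the video-rated mother-child interaction have no 52-week collection.
- **Statistical methods** lists families of methods and does not rank outcomes.

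**The concern.** Two sections of the same document answer the question of what is primary differently. The difference is not just one of detail. The longer list is headed as outcomes, is referred to as outcomes in the text below it, and predicts a difference between randomised arms on all of them. The document's own Secondary outcomes section leaves them where they are.

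What is at stake is what may be claimed at the end. A favourable result on any listed construct could be presented as a primary result by citing one section, and a null BSI-18 result could be played down in the same way. Only the BSI-18 has an effect size behind it; no effect size or event rate is given for preterm birth, infections, infant development, bonding or cortisol. The time point is open as well, and for two of the listed outcomes the end-of-study visit provides no measurement of the kind described. Settling this after the data are seen would not be credible.

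**Working it through.** **1. The plan's own figure.** Inputs from Power and sample size: d = 0.5 (7 points, so implied SD = 7/0.5 = 14), r = 0.5, alpha 0.05, power 0.80. The 27 per group reproduces as a one-sided paired t-test with dz = 0.5/√(2(1 − 0.5)) = 0.5, power 0.812. It was the only variant tried that gives 27; a two-sided comparison of two arms needs 63 or 64 per group, or 48 or 49 with ANCOVA. How 27 arose is a separate matter. Here it matters only that the calculation concerns the BSI-18 and nothing else, and that the planned 80 per arm is well above it.

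**2. Counting the list.**

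| Block | Constructs | Count |
|---|---|---|
| Women, i | stress, mental health, quality of life | 3 |
| Women, ii | self-awareness, self-confidence, self-efficacy, resilience | 4 |
| Children, i | preterm birth, birth complications | 2 |
| Children, ii | regulation disorders | 1 |
| Children, iii | cognitive, physical, psychomotor delay | 3 |
| Children, iv | infections, low birth weight | 2 |
| Both, i | interaction, bonding | 2 |
| Both, ii | maternal cortisol, infant cortisol | 2 |

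The total is 7 + 8 + 4 = 19, or 18 if cortisol counts once, in eight sub-items. This is a reader's count, not a number of tests stated in the plan.

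**3. Error rate if any one success counted (assumption).** With k independent tests at 0.05, the chance of at least one false positive is 1 − 0.95^k:
- k = 8: 1 − 0.95^8 = 33.7%
- k = 19: 1 − 0.95^19 = 62.3%

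These are upper cases, since outcomes in the same women and children are correlated. Simulated normal test statistics with an assumed common correlation give:

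| Correlation | 8 tests | 19 tests |
|---|---|---|
| 0 | 34% | 62% |
| 0.3 | 30% | 52% |
| 0.5 | 25% | 41% |
| 0.7 | 19% | 28% |
| 0.8 | 16% | 22% |

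**4. Power for the BSI-18.** Evaluable per arm: 80 × 0.9 = 72. The noncentrality is d√(n/2) = 0.5 × √36 = 3.0. With ANCOVA the effect is 0.5/√(1 − 0.5²) = 0.577, giving 3.46. Two-sided, from the noncentral t distribution:

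| Alpha | Unadjusted | ANCOVA |
|---|---|---|
| 0.05 (BSI-18 alone) | 84.6% | 93.1% |
| 0.05/8 = 0.00625 | 58.9% | 75.3% |

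The second row illustrates what keeping all eight sub-items as primary under Bonferroni would cost. The plan does not propose it, and a less conservative procedure would cost less.

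**5. Time points side by side.** The sizing assumption refers to baseline and 26 weeks. The outcome list refers to the end of the study, which under Assessments is the visit one year postpartum. In Table 1 saliva cortisol (visit samples) is taken at baseline, 8 and 26 weeks, the home samples at 8 and 26 weeks, and the interaction video at 8 and 26 weeks. Neither cortisol nor video-rated interaction can be compared at 52 weeks. In addition, from six months postpartum the intervention group is re-randomised to telemedicine or none, so a 52-week comparison mixes two treatment courses in one arm, whereas a 26-week comparison does not.

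**The case against.** The strongest reply is that the long list sits under Objectives, is worded as expectations, and gives no instrument, test or alpha. Only the sample-size section names an instrument and an error rate. One can therefore read the document as having broad primary objectives and one confirmatory criterion, with a badly chosen heading. On that reading the BSI-18 test keeps its 5% level, and this part stands.

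Three further points also stand:

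- The protocol states no rule that one significant result suffices, and it does not specify 8 or 19 separate tests. A multiplicity procedure may properly be left to an analysis plan that is not shown.
- The number of tests is undetermined. The article names no instrument for self-awareness, self-confidence or self-efficacy, while other constructs have several.
- A null result on an outcome that was not sized is not meaningless; its confidence interval can be read.

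What does not stand is that the conflict is only apparent. The section is headed as outcomes, predicts arm differences on all of (1) to (3), and is followed by a separate secondary list that omits them. An analysis plan would have to contradict one of the two statements.

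**Conclusion.** The designation of the primary outcome is contradictory as written, and so is its time point. The alpha of 0.05 and the stated power apply to the BSI-18 and give no cover to the other outcomes called primary.

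A reader might infer more: that the trial's 5% level fails altogether, that it carries a 34% or 62% false-positive risk, or that it is too small. The documents do not support this. The error rates of about 16–34% (8 tests) and 22–62% (19 tests) rest on three assumptions: separate tests at 0.05, any one counting as success, and a common correlation between 0.8 and 0. With the BSI-18 confirmed as the sole primary outcome, the level is 5%, and two-sided power at 72 per arm and d = 0.5 is 85% unadjusted or 93% with ANCOVA. The fault lies in the conflicting labels, not in the planned number of women.

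**What to change.** 1. State one confirmatory endpoint: BSI-18 total score, psychotherapy group versus stressed control group, at 26 weeks. This agrees with the correlation used for sizing, precedes the telemedicine phase, and uses a visit at which the BSI-18 is already scheduled. The choice of 26 weeks is a proposal that settles a conflict, so it should be written down as a decision.
2. State the sidedness, which the protocol does not give; two-sided 0.05 is proposed.
3. Relabel the remaining items of (1) to (3) as secondary, reported as estimates with 95% confidence intervals.
4. Replace the end-of-study wording with the visits at which each outcome is measured, in line with Table 1.
5. Move item (4) from the outcomes to the project deliverables.

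If the sponsor prefers to keep several primary outcomes, a multiplicity procedure and a recalculated sample size are needed instead.

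The cost is wording: no additional women, visits or measurements, and no change to the planned 80 per group. The downside is that the child, bonding and cortisol outcomes lose the primary label. The registry entry was not available for this review; it should be checked for agreement with the amended text.

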### Allocation

After the baseline assessment, mentally stressed women are randomly allocated to the psychotherapeutic intervention group (PIG) or the psychotherapeutic control group (PCG) with a 1:1 allocation ratio. Healthy pregnant women are assigned to the healthy control group (HCG).

Six months postpartum, women of the PIG are again randomized and receive either a subsequent telemedical intervention of 6 months duration (TIG) or not (TCG) with an allocation ratio of 1:1. An independent researcher who is not involved in the PriVileG-M trial prepares the allocation by the statistical software SAS Version 9.4 (TS Level 1 M3 Copyright© 2002–2012 by SAS Institute Inc., Cary, NC, USA) using a randomization list with simple random sampling.

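### The stated 27 women per group does not follow from the plan's own inputs for the randomised PIG–PCG comparison, which needs 64 per group two-sided (49 with baseline adjustment); the planned 80 per group is adequate

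*Protocol article*

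**What the plan says.** The section on power and sample size names the BSI-18 as the primary outcome criterion and lists its inputs. The effect is put at "d = 0.5 corresponding to a reduction by 7 points". Baseline and 26-week scores are taken to correlate at 0.5, alpha is 0.05, and the last input is printed as "a power of β = 0.80". The section concludes that "27 women are required in each group". It does not name the test or say whether alpha is one- or two-sided. It then leaves the second randomisation out of this calculation and gives a target of 80 women per group with 10% drop-out, which leaves 36 each for the two telemedicine arms.

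The comparison of interest is between arms. The Allocation section randomises stressed women to the intervention group or the "psychotherapeutic control group (PCG) with a 1:1 allocation ratio". Under Primary outcomes, "it is assumed that these outcomes differ from the control group of stressed women without intervention from those of the intervention group".

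**The concern.** A per-group size for a two-arm comparison at d = 0.5 and 80% power is usually in the sixties, or near fifty when a baseline correlated 0.5 with the outcome is used for adjustment. A figure of 27 is about half of that or less, so either the formula belongs to a different test or an input is not what it appears to be.

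The 27 is the only requirement that the article derives for the primary outcome. A reader who takes it at face value will believe that a PIG–PCG comparison with about 27 women per arm has 80% power to detect a 7-point difference. The wording of the effect adds to the doubt. It is given as a reduction, next to cited before-after reductions under psychotherapy, and the text never says whether the 7 points are a fall within one arm or a difference between two arms.

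**Working it through.** **Inputs (all from the section on power and sample size)**
- d = 0.5 corresponds to 7 points, so the implied SD is 7 / 0.5 = 14.
- r = 0.5 between baseline and 26 weeks.
- Alpha = 0.05. Sidedness is not stated, so both are computed.
- Power = 0.80 (printed as β).
- Allocation 1:1 (Allocation section).

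**Variance under r = 0.5**
- SD of change = 14 × √(2(1 − 0.5)) = 14, so change scores need the same n as follow-up scores.
- ANCOVA variance factor = 1 − 0.5² = 0.75, so residual SD = 14 × √0.75 = 12.1.

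**Step 1: can 27 be reproduced?**
Paired test within one arm: dz = 7 / 14 = 0.5. Normal approximation, one-sided: n = (1.645 + 0.842)² / 0.5² = 24.7, so 25. With the exact noncentral t distribution, n = 27 (power 0.812; n = 26 gives 0.798). The two-sided paired test needs 34. The stated 27 is therefore matched by a one-sided paired test with every printed input.

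**Step 2: the between-arm comparison**
Normal approximation: n per group = 2(z_alpha + z_power)² × v / d², with v = 1 for follow-up or change scores and v = 0.75 for ANCOVA.
- Two-sided, v = 1: 2 × (1.960 + 0.842)² / 0.25 = 62.8, so 63
- Two-sided, v = 0.75: 62.8 × 0.75 = 47.1, so 48
- One-sided, v = 1: 2 × (1.645 + 0.842)² / 0.25 = 49.5, so 50
- One-sided, v = 0.75: 49.5 × 0.75 = 37.1, so 38

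With the noncentral t distribution:

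| Analysis of PIG vs PCG | Two-sided | One-sided |
|---|---|---|
| Follow-up or change score | 64 | 51 |
| ANCOVA on baseline | 49 | 38 |

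None is 27. The most favourable, one-sided ANCOVA, is still 11 per group higher.

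**Step 3: power at the stated and planned sizes**
Noncentrality = d × √(n/2) / √v.
- n = 27, v = 1: 0.5 × √13.5 = 1.84
- n = 27, v = 0.75: 1.84 / 0.866 = 2.12
- n = 72 (80 × 0.9), v = 1: 0.5 × √36 = 3.00
- n = 72, v = 0.75: 3.00 / 0.866 = 3.46

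| n per group | Two-sided | Two-sided, ANCOVA | One-sided | One-sided, ANCOVA |
|---|---|---|---|---|
| 27 | 44% | 55% | 57% | 67% |
| 72 | 85% | 93% | 91% | 96% |

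**Step 4: other readings tried**
- Repeated-measures group-by-time interaction, two groups, two times, f = 0.25, r = 0.5: 17 per group at power 0.80, and 27 per group only at power 0.95. In this layout f = 0.25 is a between-arm difference in change of 1.0 SD. A 0.5 SD difference is f = 0.125, which needs 64 per group.
- The same interaction with three groups and five times: 27 in total, or 9 per group.
- The cited 10-point reduction used as the between-arm effect (d = 10/14): 32 per group two-sided or 25 one-sided, and 25 or 19 with ANCOVA.

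No between-arm reading at d = 0.5 and power 0.80 yields 27 per group.

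**The case against.** The strongest reply is that nothing in the trial changes. The target is 80 per group, and the 72 expected after drop-out exceed the 64 that a two-sided unadjusted comparison needs. This stands, and it limits the point to the stated figure and its justification.

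The second reply is that 64 and 49 rest on assumptions that the article does not make. Sidedness is not given, and the statistical methods section lists regression and repeated-measures analyses without fixing the primary model. This also stands, so the one-sided figures are shown beside the two-sided ones. It does not rescue 27, because every combination exceeds it.

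A reader might go on to infer three stronger things that the document does not support.
- That the authors planned an uncontrolled, one-sided pre-post test. The match with 27 is exact, but the test is not named, and a two-group interaction test also gives 27 per group, though at a power that is not the stated one.
- That natural recovery and regression to the mean would be counted as treatment effect. That would need a pre-post primary analysis, which is stated nowhere. The design is a randomised comparison, which guards against both.
- That 27 serves as a fallback minimum at which the trial would still be declared adequate. The article sets no such rule and plans no interim analysis.

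**Conclusion.** The stated requirement is wrong for the randomised comparison. Against the two-sided figures it is too low by a factor of 2.4 (64/27), or 1.8 (49/27) with baseline adjustment. Against the one-sided figures the factors are 1.9 (51/27) and 1.4 (38/27). A trial with 27 per arm would have 44% to 55% two-sided power, or 57% to 67% one-sided.

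These figures rest on the article's own d, r, alpha and power, on a 7-point between-arm difference with SD 14, and on equal arms. How 27 arose cannot be settled from the text.

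This does not show that the planned PIG–PCG comparison is underpowered. At d = 0.5 and 10% drop-out, its two-sided power is 85%, or 93% with ANCOVA. The error should be corrected because the printed justification would mislead anyone who relied on it, but it does not threaten the trial as sized.

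**What to change.** Rewrite the sample-size sentence so that it:
- names the primary test and its sidedness;
- defines the 7 points as a difference between PIG and PCG in BSI-18 total score at 26 weeks, with the implied SD of 14;
- labels 0.80 as power (1−β);
- replaces 27 with the size for that test.

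If the sponsor confirms a two-sided test, suitable wording would be: to detect a PIG–PCG difference of 7 points (SD 14, d = 0.5) at 26 weeks with two-sided alpha 0.05 and power 0.80, 64 women per arm are needed, or 49 with ANCOVA on baseline (r = 0.5); with 80 randomised and 72 analysed per arm, power is 85%, or 93% with ANCOVA. If a one-sided test is intended, this should be said, and the figures become 51 and 38.

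Allowing for 10% drop-out, the two-sided requirements are 64 / 0.9 = 71.1, so 72 randomised per arm, or 49 / 0.9 = 54.4, so 55 with ANCOVA. Both are below 80. The cost is a change of wording; recruitment and design stay as they are.
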